### Assessment

Assessments take place just before the onset of the intervention period (T0), three weeks after the intervention has started (T1) and at the end of the intervention (six weeks after start of the intervention; T2). Follow-up surveys take place 3, 6 and 12 months after the end of the intervention (T3-T5; see Table 2 for a detailed overview and the measures used at each time point). Each assessment consists of an online questionnaire and a telephone interview. The PHQ-9 is filled out weekly for monitoring purposes. The access information to the online questionnaires is e-mailed to participants automatically by the Center for Clinical Trials, at the corresponding dates after inclusion, using secure links.

### Description of outcome measures and instruments

#### Screening

The Mini International Neuropsychiatric Interview (M.I.N.I. 5.0.0) is used as a diagnostic instrument. It is a short diagnostic structured interview, used in its clinician rated version (M.I.N.I.-CR) to assess 14 psychiatric disorders according to DSM-IV. It is a valid and reliable instrument that can be applied in a reasonable amount of time with sensitivity scores ranging from .46 to .94, specificity scores ranging from .72 to .97 and a good to very good concordance between M.I.N.I. and Composite International Diagnostic Interview (CIDI), which represents the gold standard (e.g. kappa = .73 for major depressive episode [39] see [40] for a comparison to SKID).

#### Primary outcome

Primary outcome of this study is the reduction of depressive symptoms in the treatment group compared to the control condition as measured by the Inventory of Depressive Symptomatology score (IDS-SR) after the 6-week intervention. The IDS-SR is used in its German, self-rating version. The concordant validity of the German version with the Beck Depression Inventory and the Hamilton Rating Scale for Depression has been shown to be good (r > =.88) [41]. Furthermore, the scale has been shown to be useful in detecting symptom change as well as residual symptoms in depressed patients [42].

#### Secondary outcome

Secondary outcomes in this study are changes in depressive symptoms over the course of the intervention, acceptance (satisfaction with) and feasibility of the iFightDepression® tool, changes in perceived quality of life and adverse treatment effects (see Table 3).

**Table 3 Tab3:** Overview of assessment points and measurements used

Measurement time	Assessment													
	In−/exclusion criteria	Verbal consent	Sociodemographic data	Medical history, medication, therapies	M.I.N.I	PHQ-9 (Patient Health Questionnaire)	Written consent	IDS (Inventory of Depressive Symptomatology)	Content and subjective quality of guidance	Documentation AE/SAE	Evaluation of workshop/program + frequency of use	SF-12 (health related life-satisfaction)	INEP (assessment of side effects, adapted; modified for online usage)	CSQ-8 (patient satisfaction, adapted)
Online screening	P					P								
Telephone interview		P	SA	SA	SA	SA	P							
T0						P		P	SA	SA		P		
Week 1						P			SA		P			
Week 2						P					P			
T1						P		P	SA	SA	P	P	P	
Week 4						P			SA		P			
Week 5						P					P			
T2						P		P	SA	SA	P	P	P	P
T3–3 months						P		P		SA		P	P	
T4–6 months						P		P		SA		P	P	
T5–12 months						P		P		SA		P	P	

(P = patient, SA = study assistant)

Changes in depressive symptoms over the course of the intervention are measured with the nine-item Patient Health Questionnaire (PHQ-9). The PHQ-9 is a short, well validated and widely used measure, of which validity and sensitivity to change have been shown repeatedly [43, 44].

The acceptance and feasibility of the iFightDepression® tool is measured using the client satisfaction questionnaire (CSQ-8) in its German version (ZUF-8). Originally developed to measure client satisfaction with a therapy or service, an adapted version of the CSQ-8 is used to assess user satisfaction in the present study. The wording of some of the items has been adapted slightly to fit the context of web-based interventions. The internal consistency of a similar adaptation has been shown to be good (omega = .95) and ratings of satisfaction correlated with symptom reduction [45]. Four extra items, specifically designed for participants to rate different aspects of each workshop, were added. Participants also state whether they felt better after completing the last workshop and whether they attribute the change to the intervention or to other factors. Additional items at post-treatment ask participants to rate the entire intervention.

Changes in perceived quality of life are rated using the SF-12. To provide a practical short form of the SF-36, the SF-12 was developed to measure health related quality of life. The SF-12 consists of a mental and a physical component score. Its moderate to high convergent validity has been shown in several studies [46, 47].

To monitor and measure adverse treatment effects, an adapted version of the INEP (Inventory for the assessment of negative effects of psychotherapy, [48]) is used. As the original version is designed to measure adverse effects of psychotherapy, the wording of the items was changed to fit the context of IBIs. Three Items, which were not transferable, were omitted. It is a relatively new measure consisting of 18 items covering different domains (e.g. symptom deterioration, interpersonal worries or decreased compliance with other therapies). For each adverse effect, participants rate whether it was caused by the intervention or not. Adverse events (all forms of symptom deterioration or other medical conditions needing to be treated) are assessed by the study assistants during the calls using a standardized protocol. Possible association to the intervention is rated.

### Quality assurance and data management

The study is designed in accordance with the declaration of Helsinki [49]. The study development and implementation is annually supervised by a scientific international expert advisory board and adapted towards their recommendations.

Procedures for data collection have been implemented by the Center for Clinical Trials at the University of Leipzig. Research data is collected in a pseudonymized manner by the Center for Clinical Trials. Data collection for online self-report measures as well as protocols completed by study assistants are centrally administered using LimeSurvey. The questionnaires are programmed in a way that all items have to be answered. The data are stored by the Center for Clinical Trials and will be provided to the research team upon request after the last patient finishes the intervention period and at the end of the data assessment period. Regular data-backups are performed.

Phone calls as described above are carried out to improve compliance with the interventions and online self-report questionnaires are installed to measure frequency and amount of intervention use. To keep the study procedures parallel across different study assistants, Standard Operating Procedures (SOPs) were developed and all study assistants are trained on the SOPs. Every Monday the study assistants receive feedback on the participants having filled out the questionnaires including the PHQ-9 sum score to check for deterioration or suicidality. At follow-up, patients are called again and, if necessary, reminded via email to fill out the respective questionnaire to assess possible adverse events during the follow-up period and to improve completeness of data. Patients reporting acute suicidality (score > 1 on the suicidality item of the PHQ) once or symptoms indicating severe depression (PHQ < 14) for three weeks in a row in the weekly questionnaires, or acute suicidality during the follow-up period are contacted using a well-established procedure to ensure appropriate clinical support.

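### After enrolment, the only described route by which staff see PHQ-9 answers for suicidality is a weekly Monday feedback, so an answer that requires contact can wait 1 to 7 days unless the SOPs hold a faster alert

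*Protocol article*

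**What the plan says.** All of the following is in the Protocol article.

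- **Reporting line** (Quality assurance and data management): "Every Monday the study assistants receive feedback on the participants having filled out the questionnaires including the PHQ-9 sum score". Its purpose is part of the same sentence: "including the PHQ-9 sum score to check for deterioration or suicidality".
- **Contact trigger** (same section): "Patients reporting acute suicidality (score > 1 on the suicidality item of the PHQ) once". A second trigger concerns severe symptoms over three consecutive weeks. Both lead to contact under an established procedure, and no deadline is given.
- **Data system** (same section): "Data collection for online self-report measures as well as protocols completed by study assistants are centrally administered using LimeSurvey".
- **Frequency of the PHQ-9** (Assessment; Table 3): patients complete it at T0, in each of the six intervention weeks (T1 and T2 are weeks 3 and 6), and at T3, T4 and T5.
- **Staff contact** (Guidance; Assessment; Table 3): there are five calls in the intervention period. For T0 to T5, "Each assessment consists of an online questionnaire and a telephone interview". At follow-up, "At follow-up, patients are called again and, if necessary, reminded via email to fill out the respective questionnaire".
- **SOPs** (Quality assurance and data management): they exist and assistants are trained on them. Their content is not shown.

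Before enrolment the position is different, because staff give the PHQ-9 themselves in the telephone interview (Screening and consent procedure). The point therefore concerns forms completed after enrolment.

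**The concern.** The trigger and the reporting cycle run at different speeds. One answer, given once, is enough to require contact, which treats it as urgent. The step that brings answers to staff runs once a week. A patient who submits a qualifying form shortly after Monday's feedback could go almost a full cycle before anyone is due to look at it.

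What is at stake is participant safety in a fully remote trial of depressed outpatients. The trial itself collects the answer and itself defines it as requiring contact, so prompt sight of it is a fair expectation. The primary outcome, the analysis and the sample size are untouched.

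**Working it through.** The article states no response time, so there is no figure of its own to reproduce. The check has four parts.

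**1. Delay under the stated cycle.** Input: feedback every Monday. Let d = 0 for a form sent on Monday just after the feedback, d = 1 for Tuesday, up to d = 6 for Sunday. The wait to the next feedback is 7 − d days. The proposed rule is a notice acted on by the next working day, with public holidays ignored.

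| Day submitted | Mon | Tue | Wed | Thu | Fri | Sat | Sun |
|---|---|---|---|---|---|---|---|
| Monday feedback (days) | 7 | 6 | 5 | 4 | 3 | 2 | 1 |
| Next-working-day notice (days) | 1 | 1 | 1 | 1 | 3 | 2 | 1 |

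The worst case falls from 7 to 3 days. Nothing changes for Friday to Sunday. The weekday on which forms arrive is not given and they may cluster, so only the range is reported and no average.

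**2. Forms with a scheduled call.** From Table 3, with Guidance and Assessment:

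- Patient PHQ-9 forms: T0, week 1, week 2, T1, week 4, week 5, T2, T3, T4, T5 = 10.
- With a call or interview: T0, week 1, T1, week 4, T2, T3, T4, T5 = 8.
- Without: weeks 2 and 5.

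So 4 of the 6 weekly forms and 3 of the 3 follow-up forms are paired with a call. The pairing is by week or visit. No call is tied to the moment a form arrives. At follow-up, a patient who needs an email reminder can send the form after the call.

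**3. What a sum score can show.** The instrument has nine items ("measured with the nine-item Patient Health Questionnaire (PHQ-9"). Assume each is scored from 0 to a common maximum m, which the article does not give. The other eight items then total 0 to 8m.

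- Item above 1: possible sums run from 2 to 9m.
- Item at 0 or 1: possible sums run from 0 to 8m + 1.
- Sums that fit both: 2 to 8m + 1.

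The overlap is 2–17 for m = 2, 2–25 for m = 3 (24 of 28 possible values) and 2–33 for m = 4. The screening range of 5–14 lies inside it each time. A sum alone therefore cannot apply the trigger. This matters only if the feedback holds nothing else, which the text does not say.

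**4. What was still open at publication (14 March 2019).** Recruitment ended in August 2018. Assume the six-week (42-day) intervention starts at entry.

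- T5 open: 14 March 2019 − 12 months − 42 days = entry after about 31 January 2018.
- T4 open: 14 March 2019 − 6 months − 42 days = entry after about 3 August 2018.
- T3 open: 14 March 2019 − 3 months − 42 days = entry after 2 November 2018, which is after recruitment closed.
- Last T5: 31 August 2018 + 42 days + 12 months = about 12 October 2019.

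The weekly forms and T3 were very probably complete by then.

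**The case against.** The strongest case against is that alert routing and response times belong in the SOPs, which a journal article does not reproduce. What the SOPs contain is unknown and cannot be held against the plan. That stands, and it is why the delay is stated conditionally. It does not remove the point, because the article does not merely omit a route: it describes one, gives it the purpose of checking for suicidality, and fixes it at once a week.

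Other safeguards also count. Acute suicidality is an exclusion criterion and is checked at screening, every participant must already be under a physician or licensed psychotherapist (Eligibility criteria), and most forms fall in a week or visit with a call. This makes the residual risk small. It does not reach the forms of weeks 2 and 5, or a form sent after the call.

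Two stronger readings are tempting, and the document supports neither.

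- A reader might infer that staff never see the suicidality item, because only the sum score is named. The wording introduces the sum score as something included, not as the whole content, and an item-level trigger implies that the item reaches staff somehow. The weekly delay is the same whether or not the item is shown.
- A reader might infer that staff are otherwise shut out of the data until late in the trial, since stored data "will be provided to the research team upon request after the last patient finishes the intervention period". That sentence governs the release of research data. It is not a safety route and says nothing about how alerts are handled.

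**Conclusion.** The point holds as a low-priority safety improvement. After enrolment, an answer that the article defines as requiring contact can wait 1 to 7 days under the only cycle it describes. The range rests on three assumptions: forms can be sent on any weekday, Monday's feedback covers everything received up to then, and the SOPs contain no faster alert. An earlier data cut would lengthen the wait; a fixed form day close to Monday would shorten it. Confidence is medium because the third assumption cannot be checked. The document does not show that any patient was missed or that the trial lacked a suicidality procedure.

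**What to change.** Have LimeSurvey send the study assistants an automatic notice whenever a submitted weekly or follow-up PHQ-9 has the suicidality item above 1, which is the existing trigger. Require action by the next working day. Keep the Monday feedback for the remaining monitoring.

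The cost is one conditional notice in a system already in use and one line in the SOPs. The threshold, endpoints, analysis and sample size stay as they are. The real burden is that each notice has to be linked from the pseudonymised record to the participant outside the Monday routine. At publication the gain was confined to the remaining T4 and T5 forms, which already come with a telephone interview. The full benefit, including weeks 2 and 5, would go to a future trial using the same set-up.

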#### Trial status and review

The trial was registered at the German Register for Clinical Trials (DRKS) under the title “Efficacy of an internet-based self-management intervention for adult primary care patients with mild and moderate depression or dysthymia”, identification code: DRKS00009323 on 2016-02-25. International trial-registration took place through the “international clinical trials registry platform” (WHO) with the secondary ID 080–15-09032015.

This trial was reviewed and approved by the ethics committee of the Medical Faculty, University of Leipzig on 2015-03-18.

Recruitment for the trial commenced in June 2016 and was finished in August 2018.

### Statistical analysis plan

Statistical reporting will follow the CONSORT standards [50].

For the main analysis, the mixed models approach with time and intervention group as fixed factors will be used to analyze whether there is a statistically significant difference between iFightDepression® and PMR concerning depressive symptoms after the 6-week study period, measured using the IDS-SR. A random intercept and a random slope for each participant will be added if beneficial for the model fit, with the subjects being nested within groups. This method is recommended in a scenario, where repeated measures are assessed over several time points and missing values need to be handled [51, 52]. All participant that are randomly assigned to one of the conditions are entered into the analysis (intent-to-treat = ITT-analysis).

Effect sizes will be calculated for imputed data (multiple imputations with 50 imputations) taking into account the dependence of data collected within participants to avoid the loss of power due to incomplete cases [53].

The number of patients experiencing a reliable change in each group will be reported giving an estimate on improvement/deterioration not attributable to chance taking into account the reliability of the measure [54]. For this calculation the standard error at the first point of measurement (T0) will be used, because it has not yet been influenced by any intervention.

Secondary analysis will include a per-protocol analysis (PPA - including all participants who adhered to the protocol), a repetition of the main analysis with outliers excluded, and a repetition of the analysis using the PHQ-9 results and a subgroup analysis, all using mixed models. In the subgroup analyses, possible moderating variables (e.g. gender, CBT-experience or frequency and length of logins) are going to be examined.

Changes in health-related quality of life (SF-12) will be analyzed, again, using mixed models, and differences in patient satisfaction (CSQ-8) will be confirmed using a *t*-test or a Mann-Whitney *U*-test, if normal distribution is violated.

An exploratory analysis of possible adverse events (INEP and protocols of the guidance calls) will be conducted. Frequencies of the occurrence of adverse events will be reported and compared between intervention group and control group using chi-sqaured tests.

Frequency and length of logins (according to self-rating) and the amount of guidance will be reported descriptively.

Analyses will be performed using an alpha level of .05, testing two-sided. All analyses will be conducted using SPSS [55] or R [56].

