**Fig. 1 Fig1:**
[figure not shown]
Participant flow, the numbers provided are the estimates based on the power analysis and dropout percentages in previous studies [35]. (DF = depression foundation, AE = adverse event, SAE = serious adverse event, PMR = progressive muscle relaxation, iFD® tool = iFightDepression® tool)

Power analysis to determine sample size:

For the power calculation, results of the study by Hegerl et al. were used to estimate the expected difference for the primary outcome between intervention and active control group in the present study [35]. The study compared CBT to an active control condition (guided self-help group) and found a difference of 5.3 points and a pooled standard deviation of 11.1 on the IDS-C after 10 weeks. Since the present intervention takes only 6 weeks and the effect sizes might generally be smaller for online self-management compared to face-to-face treatment, we expect a difference of 4 points on the IDS-SR. The calculation was performed in G*Power (3.1.9.2) using the power analysis for independent groups. To detect this effect with a power of 80% (alpha = .05), the number of cases needed per group is 122. Considering the expected dropouts, this trial is powered for completers.

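### The primary mixed model names time and group but not the group-by-time term, the T2 contrast or the handling of T0 that its 6-week target needs

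*Protocol article*

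**What the plan says.** The Primary outcome section sets the target: "Primary outcome of this study is the reduction of depressive symptoms in the treatment group compared to the control condition", on the IDS-SR at the end of the six weeks. The Statistical analysis plan section repeats it, asking for a difference "between iFightDepression® and PMR concerning depressive symptoms after the 6-week study period, measured using the IDS-SR".

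For the model, the same section says that "the mixed models approach with time and intervention group as fixed factors will be used to analyze whether there is a statistically significant difference". On the random part it says: "A random intercept and a random slope for each participant will be added if beneficial for the model fit". It gives no criterion for benefit. All randomised participants enter the analysis.

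The Assessment section defines the visits: "Assessments take place just before the onset of the intervention period (T0), three weeks after the intervention has started (T1"), then T2 at six weeks. "Follow-up surveys take place 3, 6 and 12 months after the end of the intervention" (T3–T5). Table 3 shows the IDS at all six. The article does not say which of them enter the primary model.

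The power analysis (under Fig. 1) states that "we expect a difference of 4 points on the IDS-SR" and takes a standard deviation of 11.1 from an earlier trial. It arrives at 122 per group for 80% power at alpha 0.05, using an independent-groups comparison.

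**The concern.** A between-arm comparison of reduction at one visit is either a group-by-time contrast or a difference at that visit adjusted for baseline. The model sentence lists two factors and names neither. In a model with only main effects of time and group, the group coefficient is an average of the arm differences over the modelled visits. It equals the T2 difference only if that difference is the same at every modelled visit. If T0 is one of the responses this cannot hold under a real treatment effect, because randomisation makes the expected difference at T0 zero.

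Two things are at stake. An analyst who follows the sentence word for word tests a different and usually smaller quantity than the one the trial was sized for. An analyst who supplies the missing pieces later chooses the contrast, the role of T0 and the covariance when outcome data may already be available: under Quality assurance and data management, data can be released on request once the last patient has finished the intervention.

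**Working it through.** **Inputs from the article:** difference 4 points, SD 11.1, 122 per group, alpha 0.05 two-sided.

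**Assumptions not in the article:** true differences of 0, 2 and 4 points at T0, T1 and T2; equal variance; a common within-person correlation ρ of 0.4 to 0.7; complete data.

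**1. The plan's own figure.** SE = 11.1 × √(2/122) = 1.421, and 4/1.421 = 2.81. A two-sided t-test with 122 per group has 80.05% power (the normal approximation needs 121). The stated sample size reproduces, and this point does not affect it.

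**2. Additive model.** With complete data and a random intercept, the group coefficient is the unweighted mean of the k per-visit differences, with SD = 11.1 × √((1 + (k − 1)ρ)/k).

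- *T0, T1 and T2 as responses.* Target: (0 + 2 + 4)/3 = 2.0 points.
  - ρ = 0.4: SD = 11.1 × √(1.8/3) = 8.60, SE 1.10, power 44%.
  - ρ = 0.7: SD = 11.1 × √(2.4/3) = 9.93, SE 1.27, power 35%.
- *T1 and T2 only.* Target: (2 + 4)/2 = 3.0 points.
  - ρ = 0.4: SD = 11.1 × √(1.4/2) = 9.29, SE 1.19, power 71%.
  - ρ = 0.7: SD = 11.1 × √(1.7/2) = 10.23, SE 1.31, power 63%.
- *All six visits, effect sustained at 4 points after T2.* Target: (0 + 2 + 4 + 4 + 4 + 4)/6 = 3.0 points.

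A simulation of 40 datasets at ρ = 0.5, with T0 among the responses, gave a mean additive coefficient of 1.99 points.

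**3. Models that target T2.**

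- *Change from T0 to T2* (group-by-time contrast): SD = 11.1 × √(2(1 − ρ)).
  - ρ = 0.4: 12.16, power 73%.
  - ρ = 0.7: 8.60, power 95%.
- *T2 adjusted for T0:* SD = 11.1 × √(1 − ρ²).
  - ρ = 0.4: 10.17, power 87%.
  - ρ = 0.7: 7.93, power 98%.

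In the same simulation, the interaction model gave 4.11 points as change from T0 and 4.04 as the difference at T2. The two forms share a target but are not equivalent: baseline adjustment has more power throughout this range.

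**4. Random effects.** With equal variances, a random-intercept-only model replaces the three pairwise correlations by about their mean. The model-based SE of the T2-minus-T0 contrast is then √((1 − mean ρ)/(1 − ρ between T0 and T2)) times the true one.

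- *Constant correlation:* the ratio is 1.
- *Decaying correlation*, for illustration 0.6 between adjacent visits and 0.6² = 0.36 between T0 and T2: mean ρ = (0.6 + 0.6 + 0.36)/3 = 0.52. The ratio is √(0.48/0.64) = 0.87. The effective critical value is 1.96 × 0.87 = 1.70, so the two-sided error is about 9%.
- *Variance growth with constant correlation* leaves the error at about 5%.

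**The case against.** Naming the factors of a model is not the same as listing all its terms, and the article nowhere says that the model is additive. The sentence that names the factors also names the 6-week difference as what is to be tested, which points to a time-specific comparison. This stands. A reader might infer that the plan rules out a group-by-time term, or that it certainly averages in the pre-treatment score. The text supports neither, since it is silent on the interaction and on the role of T0.

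A journal article may leave the model equation to a fuller plan. That lowers the weight of the point but does not remove it. The section does commit to a model, in some detail elsewhere (50 imputations, the T0 standard error for reliable change), and the terms it names do not by themselves deliver the target it names.

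The power figures depend on the assumed profile and correlation, and on 122 completers. This also stands. The main analysis is by intention to treat on a planned 360. With 180 per arm (equal allocation assumed) and complete data as an upper bound, additive power is 48–60% with T0 as a response and 79–87% with T1 and T2 only. The target remains 2.0 or 3.0 points.

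On the random effects, a reader might infer that the plan inflates the type I error. The documents do not support that. Inflation needs a random intercept kept alone while correlation decays, and that is when the stated rule would tend to add a slope. What remains is that the criterion is not given.

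**Conclusion.** The point holds as a mismatch between the stated primary target and the terms named for the primary model. Run additively, no version of that model targets the 6-week difference unless the arm difference is constant over the modelled visits. That conclusion does not depend on the assumed numbers. Its size does: under differences of 0/2/4 points, ρ of 0.4 to 0.7 and 122 complete cases per arm, the test targets half to three quarters of the planned 4 points, with 35–71% power instead of 80%.

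This is not proof that the analysis will be run that way. A group-by-time model is compatible with the text and would recover about 4 points. The sample size calculation is sound on its own terms. The data-driven choice of random effects is a secondary weakness, harmful to the standard error only if within-person correlation falls off with time. It merits correction before analysis because it concerns the single primary test.

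**What to change.** State the primary model in full:

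- **Responses:** IDS-SR at T1 and T2, in all randomised participants.
- **Fixed effects:** T0 IDS-SR and its interaction with time, categorical time, group, and group by time.
- **Covariance:** unstructured within person. Drop the fit-driven choice of random effects for this test.
- **Primary test:** the adjusted group difference at T2 with its 95% confidence interval, named as the only primary test.
- **T3–T5:** secondary.

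If the sponsor prefers the change-from-T0 contrast, it should say so explicitly, since its power differs (73–95% against 87–98% under the assumptions above). The cost is wording and a few more covariance parameters. Data collection and software stay the same.

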### Randomization and allocation

All eligible participants who provide written informed consent are randomly assigned to one of the two intervention arms (see also Fig. 1). The randomization is carried out weekly by the Center for Clinical Trials (University Leipzig) using a self-developed software, using the minimization algorithm by Pocock [36] stratified for gender (male/female), depression severity (mild/moderate according to PHQ-9 during screening), and CBT-experience (present/absent) with an 80% chance using the algorithm’s recommendation to yield well-balanced groups. This procedure guarantees to keep allocation concealed for the study assistants. After allocation, blinding is not possible, because study assistants also act as “guides” for the interventions during the study. We do not consider this a risk of bias, as the results are based on self-ratings only.

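### The primary model as written uses neither the minimisation factors nor the T0 IDS-SR as covariates: it is valid, but gives up precision that costs nothing to keep

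*Protocol article*

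**What the plan says.** The section on randomization and allocation describes Pocock minimisation, "stratified for gender (male/female), depression severity (mild/moderate according to PHQ-9 during screening), and CBT-experience (present/absent) with an 80% chance" of following the algorithm. The statistical analysis plan section gives the primary analysis as a "mixed models approach with time and intervention group as fixed factors", applied to the IDS-SR after six weeks in all randomised participants. On random effects it says: "A random intercept and a random slope for each participant will be added if beneficial for the model fit". The minimisation factors are not named in this model. Two of them return as examples for the subgroup analyses, where "possible moderating variables (e.g. gender, CBT-experience or frequency and length of logins) are going to be examined"; severity is not mentioned there.

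The endpoint is worded as a change: "Primary outcome of this study is the reduction of depressive symptoms in the treatment group compared to the control condition". The IDS-SR is collected at T0, at three weeks (T1) and at six weeks (T2). The section does not say whether T0 enters as an outcome, as a covariate or as the reference of a group-by-time contrast. The sample size is an unadjusted independent-groups calculation: "we expect a difference of 4 points on the IDS-SR", with a pooled SD of 11.1 taken from an earlier trial, 80% power and 122 per group.

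**The concern.** Minimisation removes most chance imbalance on its factors. If those factors predict the outcome and the analysis ignores them, their variance stays in the residual although the design has largely taken it out of the treatment contrast. The reported standard error is then larger than the true one. Separately, differencing against T0 is less efficient than conditioning on it whenever the correlation is below 1.

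Both matter because the target effect is modest (4/11.1 = 0.36 SD), the comparator is active, and the trial is sized at 80% for completers. The stake is precision and power, not a false positive result.

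**Working it through.** **Inputs from the protocol.** Difference 4, SD 11.1, two-sided alpha 0.05, power 80%, 122 per group; 360 randomised; three minimisation factors; 80% assignment probability.

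**Assumptions, not in the protocol.** Share of IDS-SR variance explained by the three factors (R²) of 10, 20 or 30%; correlation ρ between T0 and T2 of 0.5 or 0.6; equal arms; 11.1 read as the SD of a single assessment.

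**1. The plan's own figure.** A two-sample t-test with 4/11.1 gives n = 121.85, so 122 per group, with power 80.0%. The figure reproduces, and it contains no covariate gain. The standard error is 11.1 × √(2/122) = 1.42.

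**2. Contrast on T2 level.** Adjusting for the factors multiplies the SD by √(1 − R²):

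| Assumed R² | Adjusted SE | Adjusted power |
|---|---|---|
| 10% | 1.35 | 84% |
| 20% | 1.27 | 88% |
| 30% | 1.19 | 92% |

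The unadjusted test was simulated under this minimisation in two ways:

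- 360 minimised and 244 analysed (3000 runs): type I error 4.7 / 3.6 / 2.9%, power 80 / 82 / 83%.
- 244 minimised and all analysed (1500 runs): type I error 4.0 / 3.3 / 2.3%, power 81 / 82 / 84%.

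At R² = 20%, the second simulation shows a model SE of 1.42 against an empirical SE of about 1.25 to 1.31. Adjusted type I error is near 5%. Monte Carlo error is about 0.4 to 0.6 points for type I error and 0.7 to 1.0 for power, so at R² = 10% the conservatism is barely distinguishable from none.

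**3. Contrast on change from T0.** Factor effects that are constant over time cancel in T2 − T0. In the 1500-run simulation with ρ = 0.5, the model SE is 1.42 with or without the factors, type I error is 4 to 5%, and power at R² = 20% is 80.4% without and 80.6% with them. The standard error is right and the factors add nothing.

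**4. Conditioning on T0 instead of differencing.** With σ² the variance at one assessment, the change score has variance 2(1 − ρ)σ² and T2 given T0 has (1 − ρ²)σ². The ratio is (1 + ρ)/2 after adjustment relative to differencing, written out as (1 − ρ²) / (2(1 − ρ)).

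| Assumed ρ | Ratio | Variance cut | SE, change | SE, conditioned |
|---|---|---|---|---|
| 0.5 | 0.75 | 25% | 1.42 | 1.42 × √0.75 = 1.23 |
| 0.6 | 0.80 | 20% | 1.42 × √0.80 = 1.27 | 1.42 × √0.64 = 1.14 |

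At ρ = 0.5, power is Φ(4/1.23 − 1.96) = Φ(1.29), about 90%, against 80% for change. The simulation agrees (90.1 to 90.3%).

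**5. Adding the factors once T0 is conditioned on.** Simulated power goes from 90.1 to 90.6% (R² = 10%), from 90.3 to 91.7% (20%) and from 90.1 to 92.8% (30%). The gain is 0.5 to 2.7 points.

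The second simulation used complete data, factor effects constant over time, factor prevalences of 0.3, 0.5 and 0.5, and severity carrying 70% of the explained variance. All of these are assumptions.

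**The case against.** A reader might infer that the primary confidence interval is simply too wide for the design and that power is being lost. The protocol does not support that as a general statement. The endpoint is worded as a reduction and T0 is measured. Under a change contrast the standard error is correct, and adding the allocation factors alone gains nothing unless their effects vary over time. The gains in steps 2 and 4 also belong to different contrasts and must not be added together. Nor is planned power lost: the 122 per group assumed no covariates, so the shortfall is against what could be had. All of this stands.

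It is also fair that nothing in the protocol shows how prognostic the factors are. Severity is a two-level split within a PHQ-9 range of 5 to 14, so calling it strongly prognostic would be an assumption.

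A further objection is that a condensed article names its main factors without excluding covariates, and that a fuller plan may list them. That limits the weight of the point. It does not remove it, because the section goes as far as stating fixed factors, random effects and the number of imputations, and the fixed factors stated do not reflect the allocation. If a fuller plan has the covariates, the two texts need only be aligned.

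A last tempting reading takes the two named factors literally, as a group main effect averaged over T0 to T2. That test would perform much worse (at R² = 20%, simulated power 38% unadjusted and 54% adjusted). But the section says the question is the difference after six weeks, so the stated aim does not support that reading.

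**Conclusion.** The point holds as a free improvement, not as an error that threatens validity. Type I error is not inflated under any contrast examined. Under either sensible reading of the six-week comparison, the model as written leaves precision unused:

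- **T2 level:** about 84 to 92% power adjusted against about 80 to 84% unadjusted, for R² of 10 to 30%.
- **Change from T0:** about 90% power with conditioning against 80% with differencing, at ρ = 0.5, with 0.5 to 3 further points from the factors.

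The larger and more dependable part under a change contrast is the handling of T0. The allocation factors matter mainly if levels are compared without a baseline. The direction is secure; the sizes rest on the assumed R² and ρ.

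**What to change.** Define the primary test as the between-arm difference in IDS-SR at T2, from a model that either takes T0 IDS-SR as a covariate or keeps T0 as an outcome with both arms constrained to a common T0 mean. The constrained form also keeps participants who have only a T0 value, which suits the intention-to-treat statement. Add gender, the screening PHQ-9 stratum actually used by the minimisation program, and CBT experience as fixed covariates. Do the same in the PHQ-9 and SF-12 models, each with its own T0 value.

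The cost is a few model terms. The factors were needed for allocation and T0 is already scheduled, so no new data and no change to the sample size are required. Timing is the one constraint. Recruitment ended in August 2018, and the quality assurance section allows data to go to the research team once the last patient has finished the intervention. The decision should therefore be dated and recorded before outcomes are examined by arm.
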